## Materials and methods

### Study design

This study will be a case-control study nested into a hospital-based, single-center, observational neonatal cohort. Recruited preterm neonates will be followed over their first 28 days of life. The primary clinical endpoint in this study is a blood culture (BC)-proven LOS. Secondary endpoints are clinical sepsis, NEC, death to clinical and/or BC-proven sepsis or NEC, death to any cause, or discharge from the hospital with or without sequelae.

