The calculations are based on formulae 1 for a two-sample proportions test, where *n*_*i*_ is the sample size estimated for each group, z is the normal deviation defined for the alpha level (α) and the study power (β), and *p*_*i*_ is the proportions in the respective groups.

$$n_{i}=\frac{{\left(Z\alpha /2+Z1-\beta \right)}^{2}*(p1(1-p1))+(p2(1-p2))}{{\left(p1-p2\right)}^{2}}$$
(formulae 1)

These parameters define minimal study numbers to reach power and significance. We aim to include all cases of LOS and NEC with complete microbiome and a higher number of controls, to improve the statistical power of the study, precision of the applied data analysis and allow potential subgroup analyses [19].

In the literature, the rate of positive BCs varies between study sites and is highly dependent on the quality of diagnostic procedures as well as the amount of blood transferred into BC bottles. Based on the available data and our experiences we are expecting to screen 80–100 admissions per month in the respective GA range and a study inclusion rate of 50–75%. Thus, we expect to recruit approximately 40–75 admitted newborns per month for a period of 18 months, which amounts to 720–1350 admissions over the study period. The calculations were enforced by comparing data from previous studies [7,24] and the ongoing NEST360 survey in the NCU [25], powered to identify sepsis incidence, risk factors, and mortality rates of LOS and NEC among preterm neonates.

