### Definitions of LOS, culture proven sepsis, clinical sepsis and NEC

LOS is defined as a bloodstream infection occurs after 72 hours of life, typically caused by nosocomial or community-acquired pathogens [26]. Culture-proven sepsis is identified when a bacterial or fungal pathogen is isolated from a sterile site, such as blood or cerebrospinal fluid. In contrast, clinical sepsis is diagnosed based on clinical signs and symptoms consistent with sepsis in the absence of a BC [27]. The signs and symptoms of neonatal sepsis range from nonspecific manifestations to hemodynamic collapse, requiring a high index of suspicion for timely diagnosis. This study will uniformly apply the WHO criteria for neonatal sepsis, which offer a standardized approach for identifying sepsis in preterm neonates [28]. LOS will be defined by the following criteria by responsible physicians, at least the presence of two signs as per WHO which includes difficulty feeding, convulsions, lethargy, tachypnoea, severe chest indrawing, hypothermia, hyperthermia, bulging anterior fontanelle and skin or umbilical infection with pus requiring systemic antibiotics for at least five days [28].

Cases will be categorized as culture-proven sepsis and clinical sepsis. Instances of positive BCs without accompanying signs or symptoms will be considered contaminants. Specifically, coagulase-negative staphylococci (CoNS) will be classified as a pathogen only if overt signs and symptoms consistent with sepsis, as defined by WHO criteria, are present; otherwise, CoNS will be regarded as contaminants [29]. To improve diagnostic accuracy where available, C-reactive protein (CRP) levels will be used as a biomarker during suspected sepsis episodes, with elevated levels supporting the presence of an inflammatory response [30].

In this study, NEC is defined and suspected clinically based on the presence of one or more of the most characteristic clinical features including abdominal distension, feeding intolerance, bilious vomiting or gastric aspirate and bloody stools, and if available, complemented by the finding on abdominal imaging of intramural gas, pneumoperitoneum or sentinel bowel loops [31,32].

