### Samples collection

#### Blood cultures.

To describe the etiological agents and AMR patterns of neonatal bloodstream infections, we will be collecting 1–2 ml sterile blood for cultures [35] in BD BACTEC™ Peds Plus BC bottles according to international recommendation guidelines in all participants developing signs and symptoms of LOS or NEC [36], without delaying antimicrobial treatment. For participants at risk of developing early onset sepsis (EOS), termed as presumed EOS according to standard treatment guidelines, and started on antibiotics based on risk factors, BCs will also be taken free of charge before initiation of treatment whenever possible. Another BC will be taken in cases of switching, adding, or escalating antibiotic therapy. An episode of sepsis will be classified as culture-proven sepsis or clinical sepsis depending on BC results and additional clinical information by the study physicians. The blood culture samples will be processed in the microbiology laboratory at MNH which is certified in accordance with the international standard (ISO 15189:2022).

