### Statistical analysis

Descriptive statistics will be used to summarize the demographic and clinical characteristics of the study population, including gestational age, birth weight, gender, mode of delivery, and presence of comorbidities. Mean and standard deviation or median and interquartile range for continuous variables will be used and for categorical data frequencies or proportions will be described.

To answer the first objective on the incidence and risk factors of LOS, the incidence density will be calculated as the number of new cases of LOS divided by the total person-time at risk in the cohort. The person-time at risk will be calculated by summing the individual follow-up durations until the occurrence of BC-proven LOS (clinical sepsis, NEC, and death).

Cox-proportional hazard regression will be utilized to investigate the relationship between the risk factors and risk to develop primary and secondary endpoints. First, we will perform univariate cox-regressions for potential risk factors to identify individual risk factors, all variables considered relevant for the study question will be included in the multivariate cox-regression to adjusting for potential confounders. The hazard ratios (HRs) with the 95% confidence intervals (CIs) will be estimated for each risk factor. Etiological agents of LOS/NEC and the respective AMR patterns will be described as the proportion of isolates resistant to each antibiotic and according to international standard.

Microbiome analysis will be performed to evaluate gut dysbiosis in preterm infants prior to the development of LOS and in relation to the microbiome of the mother. Association of relative abundances of microbial species with the factors of gestational age, days of life, diet, and LOS will be limited to species that were found with a non-zero relative abundance in at least 40 stool metagenomes. Square root-transformed relative abundancies will be used and analysed using linear mixed effect (LME) models, where repeatedly collected microbiome data from each child is considered to cluster.

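### Separate Cox models for culture-proven and clinical sepsis can make antibiotic exposure look falsely protective against BC-proven LOS if it lowers culture yield

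*Protocol article*

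**What the plan says.** All references are to the protocol article.

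- **Endpoints (Study design).** "The primary clinical endpoint in this study is a blood culture (BC)-proven LOS". Clinical sepsis is a separate secondary endpoint. Clinical and culture-proven sepsis are combined for death, but no combined endpoint for LOS onset is listed.
- **Allocation of episodes (Blood cultures).** "An episode of sepsis will be classified as culture-proven sepsis or clinical sepsis depending on BC results and additional clinical information by the study physicians".
- **Definition of clinical sepsis (Definitions section).** "clinical sepsis is diagnosed based on clinical signs and symptoms consistent with sepsis in the absence of a BC". The same section also gives a definition of LOS based on at least two WHO signs and then divides cases into culture-proven and clinical.
- **Model (Statistical analysis).** "Cox-proportional hazard regression will be utilized to investigate the relationship between the risk factors and risk to develop primary and secondary endpoints". An HR with 95% CI is planned for each risk factor, first univariate and then multivariable.
- **Risk factors (Table 1).** Antibiotic exposure and its type are listed among the neonatal factors. Exposure at the time of the culture is not singled out.
- **Yield (Study population and sample size).** The article accepts that culture positivity varies and is "highly dependent on the quality of diagnostic procedures as well as the amount of blood transferred into BC bottles".

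**The concern.** Secondary research question 1 asks for risk factors for LOS. A covariate that changes the chance of a positive culture also changes which endpoint an episode enters, even if it leaves the risk of sepsis unchanged. Antibiotic exposure is the obvious candidate among the listed factors, because an infant may still be on an earlier course, or have just finished one, when LOS begins. The BC-proven model would then count fewer of the exposed infants' true episodes.

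Multivariable adjustment does not help. The distortion lies in how the outcome is ascertained, and it is caused by the very covariate whose HR is being estimated. At stake is a report that antibiotics protect preterm infants against LOS when they may only suppress growth in the bottle.

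**Working it through.** **The plan's figures.** The article gives no power figure for the Cox models and no culture sensitivity. Its event count reproduces: 40 to 75 recruits a month × 18 months = 720 to 1350; 10% of these = 72 to 135 BC-proven cases. The minimum of 84 children concerns the dysbiosis comparison and is not in question here.

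**Formula.** Let T be the true HR for LOS, and s1 and s0 the culture sensitivity in exposed and unexposed infants. Splitting episodes by culture result thins the hazard:

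- HR(BC-proven) = T × s1/s0
- HR(clinical) = T × (1 − s1)/(1 − s0), provided culture-negative episodes count as clinical sepsis

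**Numbers (all sensitivities assumed).**

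| True HR | s0 v s1 | BC-proven HR | Clinical HR |
|---|---|---|---|
| 1.0 | 0.50 v 0.50 | 1.00 | 1.00 |
| 1.0 | 0.50 v 0.35 | 0.70 | 1.30 |
| 1.0 | 0.50 v 0.25 | 0.50 | 1.50 |
| 1.5 | 0.50 v 0.35 | 1.05 | 1.95 |
| 1.5 | 0.50 v 0.25 | 0.75 | 2.25 |

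**Simulation check.** Cox models were fitted to simulated cohorts of 1350 infants (half exposed, assumed 20% baseline 25-day risk of any sepsis, 100 runs per setting). With sensitivity 0.50 v 0.30 and true HR 1.0, the mean HRs were 0.58 (BC-proven) and 1.40 (clinical), against 0.60 and 1.40 from the formula. With equal sensitivity they were 0.97 and 1.01. The pooled endpoint gave 0.99 for a true 1.0 and 1.52 for a true 1.5.

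**If some clinical sepsis can never be culture-positive.** Let f be that share of the unexposed clinical-sepsis group, with the same hazard in exposed and unexposed infants. For T = 1, HR(clinical) = 1 + (1 − f) × (s0 − s1)/(1 − s0).

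- 0.50 v 0.35: f = 0.3 gives 1 + 0.7 × 0.30 = 1.21; f = 0.6 gives 1 + 0.4 × 0.30 = 1.12.
- 0.50 v 0.25: f = 0.3 gives 1 + 0.7 × 0.50 = 1.35; f = 0.6 gives 1 + 0.4 × 0.50 = 1.20.

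The BC-proven HR is unchanged.

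**Chance that a spurious effect is declared.** The probability of p < 0.05 is Φ(|ln HR| × √(d × 0.25) − 1.96), with d events and half exposed (an assumption).

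- HR 0.50: d = 72 gives Φ(0.693 × 4.243 − 1.96) = Φ(0.98) = 84%; d = 135 gives Φ(0.693 × 5.809 − 1.96) = Φ(2.07) = 98%.
- HR 0.70: d = 72 gives Φ(−0.45) = 33%; d = 135 gives Φ(0.11) = 54%.

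**The two definitions side by side.** The Blood cultures section plans a culture in every participant with signs of LOS or NEC and classifies by the result, which implies that a culture-negative episode is clinical sepsis. The Definitions section, read literally, reserves clinical sepsis for episodes without a culture. On that reading a culture-negative episode belongs to neither endpoint, the upward shift in the clinical HR disappears, and only the downward shift in the primary endpoint's HR remains.

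**The case against.** - **This could be left to the SAP.** A composite sensitivity model often is. But the article itself fixes the endpoints, the model and the covariate list, and their combination is what produces the bias.
- **An any-LOS analysis may already be intended.** The sign-based definition of LOS covers both categories, and the Statistical analysis section speaks of incidence and risk factors of LOS. This stands as an ambiguity: no such model is clearly stated, but its absence is not certain either.
- **Antibiotics at the draw are not a listed covariate.** True. Table 1 has exposure in general, so exposure that ended well before the episode dilutes the effect.
- **Cultures on treatment.** The article says "Another BC will be taken in cases of switching, adding, or escalating antibiotic therapy", which might be taken as evidence of lower yield. It is not: within an episode a further culture adds a chance of detection. For presumed early-onset sepsis, cultures are to precede treatment where possible. What remains is the infant still on, or just off, an earlier course when LOS begins, and the documents give no frequency for this.
- **Classification also uses clinical information.** True, but that does not turn a negative culture positive.
- **Blood volume.** Because "we will be collecting 1–2 ml sterile blood for cultures" allows a twofold range, a reader might infer biased HRs for volume, birth weight or gestational age. The documents do not support this. Volume is not in Table 1 and gets no HR, and nothing links the volume drawn to weight or maturity.
- **Pooling has its own bias.** The WHO signs are partly nonspecific and may arise without infection. This stands, and it is a reason not to make the any-LOS model the sole source of HRs for birth weight or gestational age.

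**Conclusion.** The point holds for antibiotic exposure. If that exposure lowers culture yield, the BC-proven HR is biased down by the factor s1/s0: a true HR of 1.0 becomes 0.70 to 0.50 under the assumed sensitivities. If culture-negative episodes count as clinical sepsis, the clinical HR is biased up, to 1.30 to 1.50 at most and to 1.12 to 1.35 when 30% to 60% of clinical sepsis could never be culture-positive. The direction follows from the algebra; the size rests wholly on assumed sensitivities, and with equal sensitivity there is no bias.

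A reader might infer that the two HRs must fall on opposite sides of 1. They need not: they move in opposite directions from the true HR, so a true HR of 2 with 0.50 v 0.40 gives 1.6 and 2.4. Nor do the documents show that the primary question is affected. The dysbiosis comparison does not use these HRs, its controls exclude any clinical or culture-proven sepsis, and it matches on previous antibiotic exposure. The weakness is confined to secondary question 1 and deserves correction before analysis.

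**What to change.** In the Statistical analysis section:

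1. Add a supporting Cox model for any LOS, defined as the first BC-proven or clinical episode after 72 hours, beside the two split endpoints. BC-proven LOS stays primary.
2. Report the proportion of LOS episodes that are culture-positive by antibiotic status at or before the draw.
3. Interpret the antibiotic-exposure HR from all three models together, and state that protection will not be claimed from the BC-proven model alone.
4. Reconcile the Definitions and Blood cultures sections so that culture-negative episodes have one defined category. This matters for item 1 too: if they fall outside clinical sepsis, the any-LOS model loses them as well and inherits the bias.

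The cost is wording and one extra model. Episodes, culture results and previous antibiotic use are already planned for capture; it should be confirmed that antibiotic status at the draw can be derived from them. The downside is that any LOS is less specific. If a share f of unexposed clinical sepsis is non-bacteraemic and unrelated to exposure, a true HR of 1.0 stays at 1.0, but a true 1.5 is diluted. With s0 = 0.50, the added hazard is k = 0.5f/(1 − f), and the pooled HR is (k + 1.5)/(k + 1): 1.41 for f = 0.3 (k = 0.214) and 1.29 for f = 0.6 (k = 0.75).

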### Variables to predict LOS and gut dysbiosis

Variables have been selected based on a literature search and local clinical experience. Table 1 shows factors predicting LOS and gut dysbiosis that will be captured during the study period. Independent variables will be categorized as socio-economic, neonatal, maternal, and septic risk factors (Table 1).

**Table 1 pone.0325099.t001:** Candidate variables for predicting LOS and gut dysbiosis.

Socio-economic factors	Neonatal factors	Maternal factors	Septic risk factors
Maternal education level	Gestational age	Age at delivery	Invasive ventilation
Self-rated household income	Sex	Parity	Central line at least 48 hrs
Family health insurance	Birth weight	Previous stillbirths	Parenteral nutrition
	Multiple births	HIV status	Presence of any maternal risk factors
	APGAR score at 1 minute	Medical conditions	Type of feeding
	APGAR score at 5 minutes	Pregnancy complications	
	Place of birth	Maternal antibiotic exposure 3 months before delivery	
	Delivery complications		
	Antibiotic exposure and type		
	Type of delivery		

During the observational period of 28 days clinical signs and symptoms of LOS and/or NEC, BC results with phenotypic identification, and antibiotic susceptibility testing, the previous use and type of antibiotics, and the clinical outcomes, will be recorded by the study team in electronic data capture forms. Stool samples for microbiome analysis will be collected in a standardized manner on day 1–3, and days 7, 14, 21 (each ±3) and neonates’ type of feeding in the last 24 hours will be categorized as exclusive human milk (no formula given), breastfed mainly (>80% feeds breastmilk/human milk), formula feed (>50% of feeds include formula), only formula (no human milk), or no enteral feeding at all.

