### Data collection tools and methods

All study data will be pseudonymously recorded and collected using password-secured tablets and managed using REDCap^®^ electronic data capture tools [33,34]. Patients will be screened for inclusion and if recruited a copy of the study admission form will remain in the patient`s file to avoid re-recruitment. Study team members will enter the data at recruitment, at times of sample collection, during each episode of sepsis or NEC, and discharge/referral or death, including information from microbial reports and other laboratory results into the eCRFs. At the end of follow-up all co-morbidities and complications will be evaluated and recorded. All data points will be checked by another study member, validated and approved by the study coordinator or local PI.

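### The Cox models make no provision for exposures that arise during follow-up, and nothing requires those exposures to precede the onset of LOS or NEC

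*Protocol article*

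**What the plan says.** The Statistical analysis section sets the model: "Cox-proportional hazard regression will be utilized to investigate the relationship between the risk factors and risk to develop primary and secondary endpoints". The sequence is then: "First, we will perform univariate cox-regressions for potential risk factors to identify individual risk factors", after which the variables judged relevant go into a multivariable model, with a hazard ratio and 95% interval for each risk factor. Person-time runs until the event. No start of the clock is given, and nothing says whether a covariate may change value during follow-up.

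The candidates come from the section on variables: "Table 1 shows factors predicting LOS and gut dysbiosis that will be captured during the study period". Many are fixed at birth (gestational age, sex, maternal factors). Others are not: "Invasive ventilation", "Central line at least 48 hrs", parenteral nutrition, type of feeding and "Antibiotic exposure and type".

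Four other statements bear on timing:
- Variables section: "the previous use and type of antibiotics, and the clinical outcomes, will be recorded by the study team in electronic data capture forms". Feeding over the last 24 hours is described together with the stool sampling schedule.
- Data collection tools and methods: data are entered at recruitment, at sampling, "during each episode of sepsis or NEC, and discharge/referral or death".
- Demographic and clinical parameters: infants are followed daily for 28 days after birth.
- End of Statistical analysis: stool samples taken after an LOS diagnosis are left out of the association tests.

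**The concern.** A Cox model compares infants at risk at the same moment, so a covariate may use only what was known by that moment. Two kinds of candidate in Table 1 can break this rule if each infant receives one summary value.

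**Immortal time.** An infant counts as having had a line for 48 hours only after reaching that point. If a line goes in on day 10, the infant qualifies on day 12. Ever/never coding then credits the exposed group with days 3 to 12, nine days in which an event would have prevented the infant from qualifying. This pulls the HR below 1.

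**Reverse causation.** Ventilation, stopped feeds and antibiotics can be responses to LOS or NEC. The article's own definitions list feeding difficulty among the LOS signs and feeding intolerance among the NEC features, and the LOS criteria mention a need for systemic antibiotics. Exposure that begins after onset but is coded as a predictor pushes the HR above 1.

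Risk factors for LOS and NEC are the first secondary research question, and the Statistical analysis section treats incidence and risk factors of LOS as its first objective. The factors a unit could act on are the ones exposed to these biases. Because the biases oppose each other, a reader could not tell the direction of error in a reported HR.

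**Working it through.** **Plan's own figures.** The article gives no event or power calculation for the Cox models. The expected events do reproduce: 0.10 × 720 = 72 and 0.10 × 1350 = 135.

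**Inputs from the article.** Cohort 1350; LOS risk from 72 hours (day 3); follow-up to day 28; 10% LOS; line qualifies after 48 hours.

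**Assumed inputs (the article gives none).** True HR 1.0; constant hazard −ln(0.9)/25 = 0.0042 per day; 30% of infants receive a line; insertion times as in the table. Each setting had 60 replicates, and results are geometric mean HRs.

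**Immortal time, ever/never coding:**

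| Share of lines placed at birth | Rest on days 1–7 | Days 1–14 | Days 1–21 |
|---|---|---|---|
| 100% | 1.00 | 1.01 | 0.97 |
| 75% | 1.00 | 0.87 | 0.86 |
| 50% | 0.91 | 0.83 | 0.73 |
| 0% | 0.80 | 0.64 | 0.50 |

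In the first row every line is placed at birth, so the three columns are repeats. A line placed at birth qualifies on day 2, before LOS risk opens on day 3, and no immortal time arises.

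**Reverse causation, ever/never coding.** Assumed: 20% exposed irrespective of LOS, three quarters of them from birth. A share r of cases is also coded exposed because of exposure after onset.

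Hand check, ignoring the small immortal-time component:
- Exposed share among cases: 0.2 + 0.8r
- Risk if coded exposed: 0.1(0.2 + 0.8r) / [0.9 × 0.2 + 0.1(0.2 + 0.8r)]
- Risk if coded unexposed: the same with 0.8(1 − r) in place of (0.2 + 0.8r), and 0.8 in place of 0.2 in the non-case term
- HR ≈ ln(1 − risk exposed) / ln(1 − risk unexposed)

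For r = 0.10 the risks are 0.028/0.208 = 0.1346 and 0.072/0.792 = 0.0909, so HR ≈ 0.1446/0.0953 = 1.52.

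| r | Hand check | Simulation |
|---|---|---|
| 5% | 1.25 | 1.14 |
| 10% | 1.52 | 1.47 |
| 20% | 2.14 | 2.17 |
| 30% | 2.92 | 2.79 |

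The result depends on the background share. A separate simulation with 15% exposed irrespective of LOS gave 1.77, 2.49 and 3.52 for r = 10%, 20% and 30%.

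**Start-stop coding.** With exposure switching on only when it qualifies, and post-onset exposure ignored, the HR was 0.93–1.04 over all settings. Simulation error is about 1.96 × [1/√(135 × 0.2 × 0.8)]/√60 = 1.96 × 0.215/7.75 = 0.05 on the log scale. The 0.93 came from the r = 5% setting and lies slightly outside that margin. The same draws also put the ever/never value there (1.14) below its hand check (1.25).

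**The case against.** The strongest reply is that the article never says these exposures are fixed. The sentence on univariable models names a method and an order, not a coding. A Cox model with time-dependent covariates is still a Cox model, and the R package named in the article supports start-stop data. A condensed article may leave coding to the full protocol or analysis plan, which are not shown. All of this is correct. A reader might infer that the plan has chosen fixed coding, but the text does not support that.

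Other parts of the reply also stand:
- Antibiotic data are described as previous use, which suggests use before the episode, although Table 1 does not repeat that limit.
- Feeding is tied to repeated sampling, so dated values may exist.
- A reader might infer that the data entry made during an episode overwrites the risk-factor value in cases. The content of that form is not shown, and it could equally serve to date exposure relative to onset.
- Mild bias would be invisible in one study. With SE = 1/√(events × p(1 − p)), 135 events and p = 0.3 give a 95% interval of a factor exp(1.96 × 0.188) = 1.4 either side. With 72 events and p = 0.2 the factor is exp(1.96 × 0.295) = 1.8.

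The reply does not remove the point. The article lists a covariate defined by duration, and others that can be responses to the outcome, for a 28-day time-to-event model with no condition that exposure come first. It recognises the problem of post-onset data for the microbiome and sets a rule there, but the rule is worded for samples and does not reach clinical exposures in the Cox models.

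**Conclusion.** The point holds in a limited form. The Cox plan does not provide for exposures that arise during follow-up, and its only pre-onset rule covers stool samples. If those exposures are coded ever/never, the HRs are biased.

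- **Line for at least 48 hours:** essentially no bias if lines are placed at birth or nearly all early; about 0.9 to 0.5 under a true HR of 1.0 as insertion moves later.
- **Exposure starting after onset and counted:** about 1.1 to 2.8 if this affects 5–30% of cases.
- **Antibiotics:** concerned only so far as the variable is not limited to previous use.

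The sizes rest on assumed exposure shares, insertion times and a constant hazard. They show what is possible and do not estimate the bias in this cohort. Because fixed coding is not stated, the documents do not support saying that the reported HRs will be biased, or in which direction overall. The expected event counts and the dysbiosis sample size are unaffected.

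**What to change.** Add to the Statistical analysis section:

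1. The time origin for each endpoint. For LOS, risk starts at 72 hours of life; infants enrolled later, as the first-week window permits, enter at enrolment.
2. Central line, invasive ventilation, parenteral nutrition, type of feeding and postnatal antibiotics are time-dependent covariates in start-stop format. Line status switches on only after 48 hours in place.
3. Only exposure that began before onset of the episode counts. Exposure starting at or after onset is ignored.
4. Birth and maternal factors stay fixed.

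The cost is some wording and a restructured dataset. Daily follow-up should make start and stop dates obtainable, and the chosen R package handles the format. The downside is that some exposure days may lack a recorded date, so a rule for these should be set before analysis. No extra infants are needed.
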